### Secondary analyses

2.28

Between group differences in infarct size and myocardial salvage as quantitative traits (% of LV) will be assessed using appropriate general linear models adjusting for initial area-at-risk (% of LV). Other continuous outcomes, including biomarkers and coronary physiology parameters, will be analyzed in a similar fashion where the assumptions of linear modelling are sufficiently met, and adjusted for baseline data. Where data are clearly not normally distributed (e.g. laboratory variables) or modelling assumptions are not met, standard transformations will be applied to address these issues. The study is designed but not powered to assess secondary and clinical outcomes. In future analyses of clinical outcomes in the longer term, they will be presented with Kaplan-Meier time-to-event curves and compared where appropriate using hazard ratios and confidence intervals from Cox proportional hazards regression.

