Health status	Assess health-related quality of life using patient reported outcome measures during follow-up, including the EQ-5D-5L, Duke Activity Status Index and Kansas City Cardiomyopathy questionnaires
Feasibility	Feasibility will be reflected by enrolment rates, procedure completion, adverse events, and patient reported experiences measures (PREMS) using a customized questionnaire.
Safety	Assessment of peri-procedural and post-procedural events as well as those during follow-up
Clinical outcomes	Assessment of clinical outcomes over 12 months and longer-term follow-up including data linkage

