### Adjudicated adverse events

2.22

Follow-up assessments for adverse events will be performed by research staff blinded to baseline data and randomization. Contacts will involve in-person visits, telephone follow-up, or review of electronic health records. Clinical events identified as potentially relevant are to be assessed by a blinded Clinical Event Committee blinded to both baseline data and randomization, according to prespecified charter. The committee will be independent of the investigators, funder, and sponsor.

During the initial hospital stay, adverse events of interest will include peripheral and cerebrovascular ischemic events and bleeding events, defined by Bleeding Academic Research Consortium (BARC) [18].

Standardized cardiovascular and stroke endpoint definitions will be used [19]. Health outcomes will include death, and cardiovascular events including MI, heart failure, stroke/TIA, and bleeding. Data on health outcomes will be collected during index admission and after hospital discharge by clinical review for all patients at 3 months and by electronic health record checks at 12 months and at the close of the study (or by letter or patient review as appropriate to ensure complete data, including for quality of life). Electronic case record linkage using the Community Health Index (CHI) number in Scotland will allow tracking of all deaths and hospitalizations (and their causes). Functional status will be assessed using validated measures: EQ-5D-5L, DASI and KCCQ.

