### Follow-up

2.24

Patient follow-up will begin from the date the first patient is recruited until 12 months after the final patient is recruited.

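### Section 2.28 names Kaplan-Meier curves for all longer-term clinical outcomes; for the non-fatal ones, cumulative incidence with death as a competing event is the better display

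*Protocol article*

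**What the plan says.** The relevant sentence closes section 2.28 (Secondary analyses). It applies to later work, "In future analyses of clinical outcomes in the longer term", and states that "they will be presented with Kaplan-Meier time-to-event curves" and "compared where appropriate using hazard ratios and confidence intervals from Cox proportional hazards regression". The qualifier about appropriateness belongs to the Cox comparison; the curves carry no such condition. The sentence just before it says "The study is designed but not powered to assess secondary and clinical outcomes".

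The outcomes are listed in section 2.22 (Adjudicated adverse events): "Health outcomes will include death, and cardiovascular events including MI, heart failure, stroke/TIA, and bleeding". Section 2.25.3 gives the same list. Neither section defines a composite that includes death, and no other estimator is named for any of these outcomes.

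On duration, Table 1 in section 2.1 plans "Assessment of clinical outcomes over 12 months and longer-term follow-up including data linkage", and section 2.24 says "Patient follow-up will begin from the date the first patient is recruited until 12 months after the final patient is recruited". With the three-year enrolment period in section 2.30, early recruits could be followed for about 3 + 1 = 4 years before any further linkage. Section 2.22 also states that record linkage captures every death, so the information needed to treat death as a competing event will be available.

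**The concern.** A patient who dies can no longer have a first heart failure admission, MI, stroke or bleed. A Kaplan-Meier analysis of one of these outcomes can handle that patient in only two ways. Death can count as an event, which turns the outcome into a composite that the article does not define. Otherwise the patient leaves the risk set at death, as if lost to follow-up. In the second case the curve describes a hypothetical population in which nobody dies first, not the proportion of patients who have the event.

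What is at stake is the meaning of a displayed curve. Section 2.26 says that results will be read by the size of estimated between-group differences, so the quantity plotted should be one a reader can take at face value. If mortality also differed between the arms, the overstatement would differ between them too.

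**Working it through.** **The plan's own figures.** The article has no event rate, death rate or time-to-event calculation to reproduce. Its only design figure is the detectable difference of 0.85 SD for NT-proBNP in section 2.27. With 51 complete participants at 2:1 (34 and 17), a two-sided 0.05 level and 80% power, the two-sample t calculation gives 0.849, so that figure stands. The present point does not bear on it.

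**Direction.** Take *n* patients under observation. Suppose *d* die without the event, and then one of the remaining *n* − *d* has it.
- One minus Kaplan-Meier, deaths removed: 1/(*n* − *d*).
- Aalen-Johansen: probability of still being event-free and alive × conditional risk = [(*n* − *d*)/*n*] × [1/(*n* − *d*)] = 1/*n*.

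The first exceeds the second when *d* > 0. If every death comes after the last event, the two agree. So one minus Kaplan-Meier is never too low, and it is too high when deaths precede later events.

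**Size.** All inputs here are assumptions. Let *F* be the value read from one minus Kaplan-Meier at the time point of interest, and *D* the mortality by then implied by the death hazard acting alone. With constant hazards over the period:
- λ₁ = −ln(1 − *F*) and λ₂ = −ln(1 − *D*)
- cumulative incidence = λ₁/(λ₁ + λ₂) × [1 − (1 − *F*)(1 − *D*)]

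Worked case, *F* = 20%, *D* = 10%: λ₁ = 0.2231, λ₂ = 0.1054, and 0.2231/0.3285 × (1 − 0.80 × 0.90) = 0.679 × 0.28 = 19.0%. The display would read 20%, which is 1.0 percentage point or 5.2% too high in relative terms.

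Cumulative incidence, with the relative overstatement in brackets:

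| 1 − Kaplan-Meier | D = 2% | D = 5% | D = 10% | D = 20% |
|---|---|---|---|---|
| 5% | 4.95% (1.0%) | 4.88% (2.6%) | 4.75% (5.3%) | 4.49% (11.5%) |
| 10% | 9.90% (1.0%) | 9.75% (2.5%) | 9.50% (5.3%) | 8.98% (11.4%) |
| 20% | 19.81% (1.0%) | 19.51% (2.5%) | 19.02% (5.2%) | 18.00% (11.1%) |
| 30% | 29.72% (1.0%) | 29.29% (2.4%) | 28.56% (5.0%) | 27.07% (10.8%) |

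The relative error is driven by mortality and hardly depends on the event risk: about 1% at 2% mortality and about 11% at 20%. At 30% mortality it would be about 18%.

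**Against sampling error.** Randomizing 56 patients 2:1 gives about 37 and 19. The binomial standard error, √[*F*(1 − *F*)/*n*], is:
- *F* = 10%: 4.9 points with 37 patients, 6.9 with 19, 4.0 with all 56.
- *F* = 20%: 6.6 points with 37, 9.2 with 19, 5.3 with all 56.
- *F* = 30%: √(0.21/37) = 7.5 points, √(0.21/19) = 10.5, √(0.21/56) = 6.1.

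The largest gap in the table is 30 − 27.07 = 2.93 points, below every standard error for that risk. For event risks of 10% to 20% and mortality of 2% to 10%, the gap is only about 0.1 to 1 point.

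**The case against.** The strongest reply is that the article does not say deaths will be censored. It lists the events collected without defining the endpoints to be plotted. Kaplan-Meier is correct for all-cause death and for any composite that includes death, and those may be the curves intended. Endpoint definitions and censoring rules are also commonly left to a full protocol or analysis plan, neither of which is shown.

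Part of this stands. Removal at death is inferred from the method, and the missing censoring rule is not itself a fault. But section 2.28 is not silent: it names one estimator for a group of outcomes that is mostly non-fatal, without the qualifier it attaches to the Cox model. An analysis plan that used cumulative incidence curves for heart failure would depart from that sentence.

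The reply on importance stands in full. These are future, unpowered analyses in a trial whose analyses are described as descriptive, and the bias is smaller than the sampling error. A Cox hazard ratio with deaths removed is already a valid cause-specific hazard ratio, so only its label is at issue.

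Two stronger readings are tempting and should not be drawn. One is that the curves must be too high as soon as any death occurs; they are too high only if events follow deaths. The other is that these curves will supply the event rates for the larger trial and make it too small. The abstract and the Discussion say only that this study should inform a larger trial with clinical endpoints. They do not say that it will be sized from these curves, or that its endpoint would be a single non-fatal outcome and not a composite with death.

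**Conclusion.** The point holds as a minor improvement to a stated method. Kaplan-Meier is named for clinical outcomes as a group. Used on a single non-fatal outcome, it cannot understate cumulative incidence and will overstate it when deaths come before later events. The direction needs no assumption about rates, only that non-fatal outcomes are plotted singly with deaths removed. The size, about 1% to 11% in relative terms, rests on assumed mortality of 2% to 20% and constant hazards, because the article gives no rates. It would grow with longer linkage as deaths accumulate. It has no bearing on the NT-proBNP analysis or the sample size.

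**What to change.** In section 2.28, replace the single statement about curves with three elements:

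1. Kaplan-Meier curves for all-cause death and for composites that include death.
2. For each non-fatal outcome (MI, heart failure, stroke/TIA, bleeding), an Aalen-Johansen cumulative incidence curve with death as the competing event.
3. Cox hazard ratios for non-fatal outcomes described as cause-specific.

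If only death and composites with death are meant to be plotted, saying so resolves the point equally well. The cost is about one sentence. Standard software fits these curves, and no extra data are needed because deaths are already captured through record linkage.

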### Trial management and governance

2.29

The study will be conducted in compliance with the Declaration of Helsinki, Good Clinical Practice and CONSORT guidelines [20].The study will be coordinated by the Study Management Group which will include those individuals responsible for the day-to-day management of the study including the Chief Investigator, Co-Investigators, and Research Nurse. Study monitoring will be conducted by monitors on behalf of NHS Golden Jubilee National Hospital Research Management Office. During monitoring assessments, Informed Consent Forms will be reviewed and source clinical data as appropriate.

### Timeline

2.30

A 3-year timeline is initially proposed for enrolling the study population. Enrolment is anticipated to progress in phases from enrolment during office hours and then to extend towards enrolment out with office-hours, 24/7, as clinically appropriate.

## Discussion

3

This prospective, randomized, sham-controlled and blinded trial will, first, test the feasibility of an exclusively radial approach to both the delivery of primary PCI, in line with clinical guidelines, and thereafter SSO_2_ therapy. In other regards, combination therapy with SSO_2_ and an intravenous glycoprotein IIbIIIa inhibitor will be delivered according to existing regulatory approvals.

The study design includes several novel features. First, this study will provide novel information on the effects of SSO2 therapy in patients with anterior STEMI using radial artery access. This novel approach for SSO2 therapy has not been previously described. The design involves a 2:1 randomization with the aim of maximizing the information on feasibility, safety and efficacy of SSO2 biradial therapy coupled with intravenous glycoprotein IIbIIIa inhibitor therapy to mitigate thrombus formation, as compared to a sham control group. The study will primarily provide information on feasibility and safety using radial artery access. This is important because femoral artery access was used in prior studies [4,5] whereas radial artery access is now recommended in clinical practice guidelines [8].

Second, by targeting a high-risk subset, patients with anterior STEMI and ischemic times of <6 h, the study will also provide novel data on the effect of SSO_2_ therapy on multisystem biomarkers of cardiovascular function. Specifically, detailed insights into treatment effect will further be provided by intracoronary physiology, CMR imaging (including estimation of absolute myocardial blood flow (mL/min/g) at 3-months using stress/rest cardiovascular MRI) and blood biomarkers (to provide multisystem insights into the potential mechanisms of any differences in infarct characteristics and LV remodeling).

Third, NTproBNP is selected as the primary outcome measure of efficacy since NTproBNP is validated for cardiac prognosis and the blood sampling approach permits serial assessments during a 3-month follow-up period, providing data on the within-subject change over time and to mitigate for the possibility of missing data on the primary outcome, should the participant not attend for a follow-up visit.

Increasing the number of sampling time points for the primary outcome mitigates the negative effects of missing data. For example, missing data are particularly problematic for paired evaluations (i.e. ×2, baseline and follow-up), which is the usual approach adopted for cardiac MRI, since missing data for just one sample rules-out paired comparisons, or any assessment of efficacy if no follow-up data are collected. Since the sample size of our trial is modest (*n* = 56), missing data would have a disproportionate effect, hence, this is mitigated by adoption of multiple sampling time points for the primary outcome.

Fourth, the final follow-up assessment is scheduled for 3-months. This time point takes account of the natural history of left ventricular remodeling post-MI (mostly established by 3-momths) balanced against the reducing likelihood of participant retention as follow-up is extended and increased costs of coordinating a clinical trial as the study duration is prolonged.

Finally, the fifth novel study design feature is participant blinding. This is achieved by implementation of a bespoke sham experience in the catheterization laboratory that is intended to mitigate the influence of bias on patient reported outcomes measures of health-related quality of life after treatment assignment. Data from this study are intended to inform a larger randomized study with clinical endpoints.

